| Project summary     | 
One third of patients presenting to Australian hospitals with ST-segment-Elevation Myocardial Infarction (STEMI) do not receive primary reperfusion treatment, which is the standard of care (1, 2). In rural and regional Australia, primary reperfusion treatment involves thrombolysis which, if delivered in timely fashion, provides outcomes similar to primary percutaneous coronary intervention (PCI) (3). Failure to provide reperfusion doubles mortality, increases length of stay and increases readmission rates (2). A high level of clinical variation, due to misdiagnosis or treatment of acute coronary syndromes (ACS), has been found in NSW. Our research in Hunter New England Health Local Health District (HNELHD) shows that missed acute myocardial infarction (MI) from failure to correctly interpret electrocardiogram (ECG) and serum markers, is common leads to increased mortality and morbidity, and is overrepresented in rural hospitals that are maintained by GPs (4).
 
This proposal will randomize small rural hospitals to either usual care or a mandated transmission of ECG and troponin from spoke (rural) hospitals to a central hub service. Protocol directed advice will be given to the randomized rural hospital clinicians, and will channel patients into the existing ACS management structures: The State Cardiac Reperfusion Strategy (SCRS) for STEMI patients, and the NSW Chest Pain Pathway for non-STEMI patients. The primary outcome will be the difference in identification of STEMI in patients who present to rural hospitals.
 
A cost-effectiveness evaluation will report the resources required to increase STEMI identification. Secondary outcomes include major adverse cardiac events (MACE) and outcomes in non-STEMI. HNELHD has a proven track record in innovation in rural cardiology. If successful and cost-effective, this project will define a new paradigm for assessment and management of ACS in rural settings,
 |

|                                                       |                                                                                                                                                                                                                                                                                                                            |

### Background and research question

Acute coronary syndromes (ACS), comprising both ST elevation myocardial infarction (STEMI) and non-ST elevation myocardial infarction (non-STEMI) are a significant cause of morbidity, mortality and cost to the community. In fact, ACS are the leading cause of mortality in Australia (5). In 2013-14 there were 104,100 hospitalisations for ACS (5). Direct hospitalisation costs are estimated at \$1.8 billion, with total economic costs around \$17.9 billion annually (6). People in rural and remote areas are 60% more likely to be hospitalised with ACS than people in major cities, and the mortality rate is also higher (5). Rural patients hospitalised for ACS often require hospital transfers, which add further burden on the ambulance and hospital systems and local community. Timely access to evidence-based and optimal ACS management, in both the acute and chronic phases of ACS, is imperative for optimal clinical care (7).

The failure to treat ACS, in particular STEMI, is a significant issue nationally. In the Snapshot-ACS study, failure to treat STEMI occurred in 36.8% of patients (1). Failure to treat in the acute phase resulted in a doubling of mortality (2). This preventable mortality, due to clinical variation, was not able to be more accurately quantified within the study design of Snapshot-ACS, but there are clearly medical, social and economic costs associated with suboptimal treatment of ACS.

Local causes for failure to treat STEMI in HNELHD have been collected after a systematic review of ACS avoidable deaths from the Clinical Excellence Commission in NSW. Local data has been systematically collected to better identify the problems inherent in treating ACS in the rural environment (4). The data shows a high incidence of misdiagnosis of STEMI in smaller, rural hospitals with a consequent increase in mortality. The missed acute myocardial infarction (MAMI) data indicates that failure to interpret the ECG and confused clinical judgment are the most frequent causes of failure to treat STEMI, occurring in 70% and 65% of missed STEMI cases respectively (4). We therefore propose to support diagnosis and clinical decision making in smaller rural hospitals to prevent missing the diagnosis of STEMI.

**Aims:** To improve identification and management of patients with ACS in rural hospitals across 3 LHDs by implementing a hub and spoke ACS management system.

**Research Question:** In patients admitted to a rural hospital with suspected ACS, does a centralised management system improve identification of STEMI and subsequent clinical outcomes in all ACS patients?

### **Hypotheses:**

1. The MORACS program will improve identification of STEMI
2. The MORACS program will improve 30-day mortality, 12-month mortality, time to reperfusion, length of hospital stay and readmission rates in patients with suspected ACS presenting to rural hospitals

Our proposal addresses a variation in clinical care that is deadly, costly, potentially preventable. Hub-and-spoke models have been shown to be effective in other clinical situations, but our application is a novel use of this approach. Our telehealth solution to this clinical issue will maximise the clinical support to many rural hospitals.

The NSW State Cardiac Reperfusion Strategy (SCRS) aims to deliver increased access to medical advice and reperfusion therapies in a timely manner for patients diagnosed with STEMI. Our approach is complementary to the SCRS and will in no way overlap with this. We aim to assist clinicians earlier in the diagnostic work-up, to prevent the diagnosis being missed. If a diagnosis of STEMI is made, the patient will be treated via the usual SCRS process.

Research design and methods (maximum 4 pages)

**Study design:** A prospective, cluster randomised controlled trial (RCT) to evaluate the effectiveness of a hub and spoke ACS management system to improve health outcomes for rural residents.

**Setting:** Hunter New England Local Health District in regional/rural NSW Australia. The following hospitals will be included:

Armidale, Barraba, Bingara, Cessnock, Denman, Dungog, Glenn Innes, Gloucester, Gunnedah, Guyra, Kurri Kurri, Merriwa, Moree, Murrurundi, Muswellbrook, Narrabri, Nelson Bay, Singleton, Scone, Tenterfield, Vegetable Creek, Walcha and Wialda;

These hospitals were selected because General Practitioners (GPs) or Career Medical Officers (CMOs) manage cardiology admissions, i.e. there are no Emergency Medicine specialists at these hospitals. Together they assess over 6000 chest pain presentations per year. The rationale for including GP and CMO staffed hospitals was that these were the hospitals with higher numbers of missed myocardial infarctions in our prior study (4).

**Participants:** All patients presenting with chest pain for investigation to hospitals from rural and remote communities throughout the HNELHD. Notably, patients with prehospital ECGs performed by ambulance paramedics showing STEMI will NOT go through this process, they will go via existing SCRS pathways. All patients presenting to Emergency Departments, whether by self-transport or via ambulance without a prior STEMI diagnosis, will be included.

**Eligibility:** Inclusion criteria – Hospitals where GPs or Career Medical Officers (CMOs) manage ACS presentations will be included. All consecutive patients presenting to hospital with suspected ACS (eg. chest pain for investigation or other heart related symptoms such as shortness of breath or who are triaged as possible ACS) will be included.

Exclusion criteria – Hospitals staffed by Emergency Medicine specialists (FACEMs) will not be included. Our data suggest the rate of missed STEMI in these hospitals is low. There will be no patient-level exclusion criteria.

**Randomisation:** Hospitals will be randomised to receive the intervention (MORACS) or control (usual care). Randomisation will be undertaken independently by personnel from the HMRI statistical support unit. Randomisation will be stratified based on hospital size and medical staffing. Rural hospitals included in the study have bed numbers that range from 0 to 100. In most rural hospitals admissions are managed by on-call GPs where the GP attends as required. In a small number of rural hospitals admissions are managed by CMOs who are staffed 24 hours per day, therefore potentially able to offer more timely treatment. GP vs CMO staffing will be separately stratified to better identify different outcomes of care driven by differing medical management system in place.

**Allocation to treatment:**

Intervention arm - All patients presenting to an intervention hospital will have an ECG and serum troponin level result transmitted to a central reporting service based at John Hunter Hospital. This service is monitored by the Department of Cardiology at John Hunter Hospital. Staff with clinical expertise from the central reporting service will review the ECG and serum troponin level and determine the likelihood of an acute coronary syndrome. The central reporting service will contact the hospital with diagnostic support and advice on which evidence-based pathway to follow – the SCRS for STEMI or the NSW Chest Pain Pathway for non-STEMI. This utilises existing evidence-based pathways, rather than providing *ad hoc* advice on individual patient management. The service will be staffed by the clinical cardiac liaison officer of John Hunter Hospital on weekday morning shifts and by a dedicated afternoon shift and weekend clinical nurse consultant. Overnight will be staffed by the John Hunter CCU charge nurse. There is considerable experience at John Hunter Hospital with reading pre-hospital ECGs and discussing cases with the ambulance personnel who transmitted the ECG, as part of the SCRS. This project will extend this approach into rural hospitals and will also incorporate the results of troponin testing, thereby capitalising on existing expertise. This will facilitate expert ECG reading, even when the algorithm does not detect STEMI, as well as helping clinicians identify high risk ACS.

Control arm- Will continue with current practice and treatment processes which will consist of management of patients without supportive expert advice, except where this is requested as part of normal process.

**Communication between referral hospital and central reading service:** Using the iPIMS patient registration system, an automated notification to the reading clinician is generated when anyone is triaged with diagnoses compatible with acute coronary syndromes. All ECGs and point of care troponins are available on the centralised medical record (Clinical Applications Portal - CAP). The reading clinician will contact the rural hospital emergency department and will discuss the case with the treating clinician, whilst able to simultaneously view the results of troponin and ECG on CAP.

**Follow-up:** All patients will have outcomes data recorded at hospital discharge or hospital transfer in the medical record. Thirty-day and 12-month readmission rates (and reasons) will be identified through the Centre for Health Record Linkage (CHeReL). Deaths will be identified through the National Death Index. No individual patient follow-up will be performed.

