#### **Outcomes:**

Primary Outcome: Proportion of correctly identified STEMI. ECGs will be adjudicated by a senior clinician at John Hunter Hospital in consultation with the treating clinician who has assessed the patient. All ECGs performed on all patients presenting with possible ACS will be analysed. In HNELHD, this will be performed via CAP online.

Secondary outcomes: In-hospital, 30-day and 12-month mortality, time to reperfusion (for STEMI), length of hospital stay, MACE (major adverse cardiac events: death, repeat MI or all-cause readmission) at 30-days and 12-months. Post discharge health care utilisation and medication adherence will likely be improved by better hospital care, so we will assess this by MBS and PBS linkage. Myocardial infarction will be defined by elevated troponin in the context of typical ischaemic symptoms. Mortality will be ascertained from the National Death Index (NDI). Readmissions will be captured by CHeReL. Reperfusion and revascularisation data will be ascertained from the Cardiac and Stroke Outcomes Unit in HNE.

**Measures:** Primary and secondary outcome data will be obtained from medical records and from CHeReL. We have discussed the project and received a formal quote from CHeReL. We will also link with MBS and PBS to assess post-discharge healthcare utilisation and medication prescription/adherence after hospitalisation. This will contribute valuable qualitative information as well as informing cost effectiveness analysis.

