**Considerations about Aboriginal and Torres Strait Islander Peoples:** Aboriginal and Torres Strait Islander Peoples have disproportionately higher rates of ACS, and these occur at a younger age than in non-Indigenous people (8). In rural settings, Aboriginal and Torres Strait Islander Peoples make up a higher percentage of the population. Our project has been thoroughly discussed with and reviewed by the Aboriginal Health Unit of the HNE LHD. Improving diagnosis, management and outcomes for rural ACS patients will disproportionately advantage Aboriginal and Torres Strait Islander Peoples.

**Implications for Ambulance:** NSW ambulance service (NSWAS) have been consulted and are a partner for this project. Existing ambulance work flows will not be changed. With increased diagnosis of STEMI, there will be a higher rate requirement for urgent transport to a Primary PCI centre, under the SCRS. It is estimated this will be an additional 60 STEMI patients over the 15 months recruitment period. Ambulance will benefit from earlier notice of transfer in non-STEMI patients, which will improve workflow. Ambulance have requested data on outcomes to inform their practice, and we will provide data on ambulance transported patients back to NSWAS.

**Governance structure:** The project will be supervised by the MORAC steering committee. The steering committee will comprise project investigators, partner representatives, clinicians, operational managers, clinical stream and clinical governance representatives and will meet bi-monthly.

There will be two distinct working groups operating under the steering committee: the research working group and the system implementation group. Both groups will report to the MORAC steering committee.

The research working group will be chaired by the Chief Investigator and will have membership of senior academic staff who will monitor the ongoing design and implementation of the project. This group will meet on a monthly basis.

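### Recording outcomes at transfer exposes length of stay and in-hospital death to an artefact that differs by arm, because the intervention is expected to raise transfers

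*Protocol*

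**What the plan says.** All references are to the protocol.

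- **Follow-up** sets the recording point: "All patients will have outcomes data recorded at hospital discharge or hospital transfer in the medical record". The same paragraph takes 30-day and 12-month readmissions from CHeReL linkage, and adds "Deaths will be identified through the National Death Index".
- **Outcomes** lists in-hospital mortality and length of hospital stay among the secondary outcomes, together with "MACE (major adverse cardiac events: death, repeat MI or all-cause readmission) at 30-days and 12-months". It adds "Readmissions will be captured by CHeReL", and names medical records and CHeReL as the sources of primary and secondary outcome data.
- **Hypotheses**, item 2, counts length of hospital stay and readmission among the things that the programme will improve.
- **Implications for Ambulance** states "With increased diagnosis of STEMI, there will be a higher rate requirement for urgent transport to a Primary PCI centre, under the SCRS", and then "It is estimated this will be an additional 60 STEMI patients over the 15 months recruitment period".

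No section says whether a transfer ends the index stay, whether length of stay and in-hospital death extend to the receiving hospital, or whether the receiving hospital's admission is left out of all-cause readmission.

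**The concern.** The only recording point given for in-hospital outcomes is discharge or transfer, whichever ends the stay at the rural hospital. The protocol itself expects the intervention to change how often transfer happens. An endpoint cut at an event that treatment affects can differ between arms with no difference in health.

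- **Length of stay.** Days spent at the receiving hospital are not counted, and more patients lose such days in the intervention arm. The error runs in the direction that Hypothesis 2 predicts.
- **In-hospital death.** The death itself is found through the National Death Index. Whether it counts as in-hospital depends on where the episode ends. If it ends at transfer, deaths at the receiving hospital drop out, more often in the intervention arm.
- **Readmission and MACE.** Here the risk is miscounting, not loss of data. If the receiving hospital's admission appears in the linked data and all-cause readmission is read literally, a successful referral becomes an adverse event, which counts against the intervention.

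**Working it through.** **Inputs from the protocol** (Power calculation, Implications for Ambulance): 6,300 presentations a year; STEMI 5%, about 315 a year; missed STEMI 36% versus 20%, so identified STEMI 64% versus 80%; recruitment of 15 months; equal arms; 60 additional STEMI patients needing urgent transport.

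**Step 1. The plan's own figure of 60.**
- STEMI over 15 months: 315 × 15/12 = 393.75.
- Extra identified if every hospital had the intervention: 393.75 × 0.16 = 63.0.
- Extra identified with half of the patients in intervention hospitals: 196.875 × 0.16 = 31.5.
- On the planned 338 patients: 338 × 0.16 = 54.1, or 169 × 0.16 = 27.0 in one arm.

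The 60 is not reproduced exactly. It lies near the all-hospitals figure and is about twice the one-arm figure. The difference between arms that follows from the plan is therefore about 27 to 32 patients. Putting all 60 in the intervention arm would give 60/196.875 = 30.5% of its STEMI patients, which exceeds the planned 16 points. The steps below use 31.5, or 16 points.

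**Step 2. Share transferred.** The protocol gives none. Let *t* be the excess probability of transfer for an identified over a missed STEMI, assumed to lie between 25% and 100%. A missed STEMI that is transferred anyway lowers *t*.

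**Step 3. Readmission or MACE, if a transfer is counted as an event.** Among STEMI the artefact is 16 points × *t*. Over all suspected ACS it is 5% of that; as a check, 31.5/3,937.5 = 0.8%.

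| *t* | STEMI (points) | All suspected ACS (points) |
|---|---|---|
| 25% | 4 | 0.2 |
| 50% | 8 | 0.4 |
| 75% | 12 | 0.6 |
| 100% | 16 | 0.8 |

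**Step 4. Length of stay, if it stops at transfer.** Let *d* be the mean days after transfer, assumed to be 1 to 5. The between-arm artefact in mean STEMI stay is 0.16 × *t* × *d*.
- *t* = 100%: 0.16 × 1 = 0.16 days to 0.16 × 5 = 0.80 days.
- *t* = 25%: 0.04 to 0.20 days.
- Over all suspected ACS at *t* = 100%: 0.05 × 0.16 = 0.008 days to 0.05 × 0.80 = 0.04 days.

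**Step 5. In-hospital death, if it stops at transfer.** As an illustration, assume true mortality of 8% in both arms, with half of the deaths in transferred patients falling after transfer. Neither figure is in the protocol. Assume also that missed STEMI are not transferred. Deaths left out of the count:
- *t* = 100%: control 8% × 0.64 × 0.5 = 2.56%; intervention 8% × 0.80 × 0.5 = 3.20%; difference 0.64 points.
- *t* = 25%: 0.64 × 0.25 = 0.16 points.
- Over all suspected ACS at *t* = 100%: 0.64 × 0.05 = 0.03 points.

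If every death were otherwise in hospital, the recorded rates at *t* = 100% would be 5.44% versus 4.80%, a ratio of 0.88 with no true difference.

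Possible effects through non-STEMI transfers, about 15% of patients, are not quantified, because the protocol gives no change in their number.

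**The case against.** The strongest reply is that the Follow-up sentence describes what goes into the medical record, and that the sentences after it name other sources. On this view the plan is merely silent on a derivation rule, and joining contiguous stays is work that a statistical analysis plan, not shown here, may well specify. Much of this stands. A reader might infer that outcome capture stops at transfer altogether. The documents do not support that: deaths come from the National Death Index and readmissions from CHeReL, so nothing is lost for 30-day or 12-month mortality. Nor does the protocol say that a transfer counts as a readmission. What remains is that it states a recording point that includes transfer, and names no other endpoint for length of stay or in-hospital death.

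A second reply is that the net direction is not established, since a missed STEMI may be sent home early and die there. That is fair for the observed difference between arms, and for the ratio of 0.88. It does not touch the artefact itself: given more transfers, more days and more deaths go uncounted in the intervention arm.

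A third reply concerns size. The 16 points need all identified and no missed STEMI to be transferred, and apply to STEMI only, whereas Hypothesis 2 concerns all suspected ACS. This is accepted; the figure is a ceiling.

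Finally, a reader might infer that the cost-effectiveness result is distorted. That is mostly relabelling. A receiving-hospital stay logged as a readmission is still costed, and the measure of effect is STEMI identification. The readmission counts in the cost-consequence analysis would carry the wrong label.

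**Conclusion.** The concern holds for length of stay and in-hospital mortality. As written, both are exposed to an artefact that differs by arm, because recording ends at an event that the protocol expects the intervention to increase. Exposed is the right word: a reader might conclude that these outcomes are biased, but that depends on episode definitions that the protocol does not give. For readmission and MACE the exposure is conditional on counting the receiving hospital's admission.

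The possible distortion is material among STEMI patients and small over all suspected ACS. The ranges in the working rest on assumed values for the excess share transferred, the days after transfer and, for in-hospital death, the mortality level and its timing. The primary outcome and 30-day and 12-month mortality are untouched, so this is a point about secondary outcomes.

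**What to change.** Add to Outcomes a definition of the index episode: all contiguous hospital stays from first rural presentation to final discharge, including inter-hospital transfers. Measure length of stay and in-hospital death over that episode. Count readmissions, including those within MACE, only after final discharge, so that a transfer is never a readmission. Amend the Follow-up sentence to agree.

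The episode can be built from the planned CHeReL linkage, for which the protocol reports a formal quote, provided that the extract covers receiving hospitals; this should be confirmed before the request is finalised. No new patient contact or form is needed. The downside is a little extra linkage work. The definition should be fixed before outcome data are seen by arm.
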